Vaping has also been associated with psychological and mental health concerns. In a study of university students, the use of e-cigarettes (devices that turns liquid containing nicotine into vapor) was found to be associated with multi-drug use, including alcohol and opioids, low self-esteem, symptoms of attention-deficit/hyperactivity disorder, post-traumatic stress disorder, gambling disorder, and anxiety. E-cigarette use was associated with traits of impulsivity and internalizing and externalizing problems. There is likely a bidirectional association between vaping and mental health. Studies showed higher depression and stress scores were predictive of e-cigarette use in college students. These findings highlight the co-occurrence of vaping with mental health challenges and problematic substance use in non-psychiatric populations. Further, these studies highlight the need for investigating vaping behaviour in a high-risk population, and specifically in the context of the opioid epidemic within the current COVID-19 pandemic where vulnerable groups are expected to bear the brunt of the epidemic within the pandemic.

We completed a systematic review of vaping within OUD population and found that some research has suggested that vaping may be associated with adverse outcomes including increased psychiatric distress and physical health symptoms such as coughing and headaches. However, there is no research examining vaping and COVID-19 related symptoms in the OUD population.

Preliminary data from our study investigating pharmacogenetics of OUD in patients receiving medication-assisted treatment (MAT) (POST study, a CIHR funded cohort study, n=2,360, individuals 16 years and older, 56% men) showed 19.2% of individuals with OUD use vaping, with 74% of participants vaping nicotine, 33% vaping cannabis (THC, CBD, Marijuana and shatter), 11% vaping of both cannabis and nicotine, and 5.5% reporting vaping water or “flavour”. The POST Study collected information pertaining to initiation of opioid use, opioid addiction treatment history, cannabis use, illicit drug use, and physical and mental health symptoms, using a set of questions and validated clinical questionnaires. Specific information pertaining to vaping behaviour has also been collected. Participants were asked

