## **7.0 Study Methods**

We will conduct qualitative interviews on the phone to obtain information on the perceptions of vaping and vaping behaviour patterns (i.e., reasons for vaping, type of substance, effect of vaping on health) in the OUD population. With the expertise of a qualitative expert, we have designed an unstructured interview guide (see attached interview guide) that have 8 broad, open-ended questions that will allow the interviews flexibility of asking more tailored questions as the participant shares their thoughts and experiences. The qualitative interviews will be audio recorded and transcribed without any identifying information.

In addition to the qualitative interview, we will also administer a Questionnaire of Vaping Craving (QVC), a short validated questionnaire for assessing vaping beliefs and behaviours, and collect demographic details. We will also be collecting urine drug screen results for opioids, cocaine, amphetamines, cannabis and benzodiazepines from medical records for a period of 12 months after study enrolment.

Participants will be provided with a \$10.00 Tim Hortons gift card for their participation.

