## **11.0 Sample size**

Based on the qualitative literature, it has been suggested that one should only conduct qualitative interviews to the point of saturation, that is until no longer obtaining different perspectives. It has been suggested that for observational studies, between 30-50 participants is the recommendation. The sample size for this study is 50 participants.

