### **16.0 Statistical analyses**

Data for this aim will be analyzed using Nvivo 12 qualitative data analysis software (QSR International). The free-text data will be run through a word frequency query to logically arrange the information and determine the most common words. The word count query will help identify initial patterns in the data; there is evidence that this function improves analytic accuracy when compared to manual qualitative word frequency analyses.

In order to avoid decontextualization of the free-text answers, the minimum number of letters permissible in the word frequency query will be set to four. Any word with a frequency weighting of greater than 0.5% will be coded as a node. A node is a collection of references found in the free-text data that corresponds to a particular theme or word. Words with a word frequency percentage above 0.5% that are related to a similar theme will be grouped in the same node. From this output, we will employ matrix coding queries. The output of a matrix coding query is a chart that displays the number of references coded at each node and the corresponding demographic attributes for each participant.

The thematic data will be presented for the overall population, by sex, gender, type of MAT, age, and ethnicity.

Additionally, with the urine drug screen results from the medical records, we will conduct linear and logistic regressions to see if there are any differences between socio-demographic variables and substance use outcomes in this population. We will need to see the distribution of the outcomes to decide on whether a linear or logistic model will be appropriate.

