### **18.0 Harms**

This study is a minimal risk non-pharmaceutical study; however, there may be risks involved. The participant may feel upset or distressed when asked about when asked about vaping

behavior. The research assistant will attend to the participant needs and remove them for the study or skip over certain questions if needed.

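### The theme matrix counts references with no participant count or subgroup denominator, so its figures can be dominated by repetition and will scale with subgroup size

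*Protocol*

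**What the plan says.** Protocol section 16.0 names the counting unit at each step of the thematic analysis.

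- Creation of a node depends on word frequency in the pooled text: "Any word with a frequency weighting of greater than 0.5% will be coded as a node". No minimum number of speakers is set.
- A node is defined by mentions: "A node is a collection of references found in the free-text data that corresponds to a particular theme or word".
- The matrix output is "a chart that displays the number of references coded at each node and the corresponding demographic attributes for each participant".
- Presentation follows: "The thematic data will be presented for the overall population, by sex, gender, type of MAT, age, and ethnicity".

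Nowhere does the protocol give a count of participants per node, a denominator for a subgroup, a limit on references per participant or an adjustment for transcript length.

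Two other sections bear on how much each person will contribute. Section 7.0 describes an unstructured guide with "8 broad, open-ended questions that will allow the interviews flexibility of asking more tailored questions as the participant shares their thoughts and experiences". Section 18.0 allows the research assistant to "skip over certain questions if needed". Section 11.0 fixes the size: "The sample size for this study is 50 participants".

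**The concern.** A reference is one coded mention. One participant can supply many references to one theme, and the interview format makes unequal contributions likely: follow-up depends on what the person says, and some questions may not be asked at all. A count of references therefore mixes how many people raised a theme with how often each returned to it.

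The same count, shown by subgroup without a denominator, also carries the size of the subgroup. A larger group produces more references to every theme even if its members say the same things as the smaller group.

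At stake is the main descriptive output of the study. The primary objective (section 6.1) is to understand perceptions and motivations for vaping in patients treated for OUD, and section 10.0 sets no structured primary outcome. The node and matrix tables are then the stated numerical summary of the primary aim. A reader of those tables could take a theme pressed by a few people for a common one, or a difference in group size for a difference in views.

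**Working it through.** **Figure to reproduce.** There is none. Section 11.0 rests the 50 participants on saturation and a literature range of 30-50, and no precision or effect size is stated for the thematic counts. The check is therefore of what follows from the stated counting unit.

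**Inputs from the protocol.** N = 50 (section 11.0). Node threshold 0.5% of word frequency (section 16.0). Counting unit: references (section 16.0).

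**Inputs assumed.** Mentions per person, transcript lengths and subgroup sizes. The protocol gives none of these. The 56% used once below comes from the description of the sponsor's earlier cohort in section 5.1 ("n=2,360, individuals 16 years and older, 56% men"). It is not a quota here, and it does not describe only the people in that cohort who vape.

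**1. Repetition.** References = participants raising the theme x mentions per participant.

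| Theme | Participants | Mentions each | References | Participants as % of 50 |
|---|---|---|---|---|
| A | 5 | 5 | 25 | 10% |
| A | 5 | 6 | 30 | 10% |
| B | 25 | 1 | 25 | 50% |

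At five mentions each, A ties with B. At six, A has the larger count although one fifth as many people raised it.

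**2. Subgroup size.** With the same mean number of references per person, r, in both groups, the ratio of raw counts is (n1 x r)/(n2 x r) = n1/n2.

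- 0.56 x 50 = 28, leaving 22: 28/22 = 1.27
- 35/15 = 2.33
- 45/5 = 9

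The ratio is the same for every theme, so the order of themes within a group is unaffected. Only the comparison of raw totals between groups is distorted.

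**3. Concentration of talk.** Let w be each participant's relative volume of references, drawn from a lognormal distribution (assumption; 4,000 simulated samples of 50). The effective number of participants is (sum of w)^2 / (sum of w^2).

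| Log-SD of w | Share from the 10 most talkative | Effective number |
|---|---|---|
| 0.3 | 29% | 46 |
| 0.5 | 36% | 40 |
| 0.8 | 47% | 29 |
| 1.0 | 55% | 22 |

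This shows how far the total can rest on a minority. It does not by itself reorder themes. For that, the talkative participants must also dwell on different themes from the rest.

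**4. Node threshold.** If k participants each speak L times as much as each of the others, their share of the text is kL/(kL + 50 - k). To create a node by themselves they need a word at a rate of 0.005/share in their own speech.

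- k = 1, L = 1: share 1/50 = 0.02, rate 0.005/0.02 = 25%
- k = 5, L = 1: share 5/50 = 0.10, rate 5.0%
- k = 5, L = 3: share 15/60 = 0.25, rate 2.0%
- k = 5, L = 5: share 25/70 = 0.357, rate 1.4%

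One participant of ordinary length would rarely create a node alone. A handful of long talkers could do so more easily. The weight of the point lies in steps 1 and 2.

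**5. Counting participants instead.** Use participants with at least one reference, divided by the group n. In step 1, A becomes 5/50 = 10% and B 25/50 = 50%, however often anyone repeats a theme. In step 2, if half of each group raises the theme, 14/28 = 11/22 = 50%, and the 1.27-fold gap disappears.

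**The case against.** The case for leaving the text alone has five parts.

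- **No ranking or testing is planned.** Section 16.0 says what a matrix query displays and that themes will be presented by subgroup. A reader might infer that themes will be ranked by verbosity, or that raw counts will be compared formally across groups and so yield spurious differences. The protocol says neither, and word counts are described as a help in finding initial patterns. This stands: the fault is in what the table shows, not in a stated inference.
- **The information is already there.** The chart carries each participant's attributes, so participant counts could be derived, and table layout is commonly left to an analysis plan. This stands in part. It makes the remedy cheap, but the protocol has itself chosen references as the unit, so the point is about a stated method and not only an unstated layout.
- **References have a use.** The study is qualitative and is not designed to estimate how common a view is. Repetition can show how much a theme matters to a person, which a yes/no count per participant loses. This stands, and is a reason to keep references beside participant counts.
- **Participant counts have a weakness too.** Not everyone is asked the same questions, so silence on a theme is not absence of the view, and longer interviews give more chances to mention it once. This stands and limits how the percentage may be described.
- **The magnitudes are illustrative.** The splits and talkativeness values are assumed, and a report that gives group sizes would expose the subgroup effect. This stands for the size of the effect. The direction follows from the counting unit.

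**Conclusion.** The point holds in a limited form. As written, section 16.0 displays mentions, without the number of people behind them or the size of each subgroup. Such counts can be dominated by a few participants who repeat a theme, and they scale with subgroup size when views are identical. The first result needs only unequal repetition, which the interview format makes likely. The second needs only unequal groups with the same mean number of references per person.

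The actual size of either effect cannot be computed from the protocol, because it depends on transcripts and subgroup numbers that do not yet exist. The documents do not support saying that talkative participants will determine the reported themes, only that they can dominate the counts. This is a low-cost improvement to the descriptive tables. It does not put the feasibility of the study or its qualitative interpretation in doubt.

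**What to change.** Amend section 16.0 so that, for each node, the matrix reports the number and percentage of participants with at least one reference, overall and within each subgroup, with the subgroup n shown as the denominator. Keep the reference count in an adjacent column, labelled as a measure of emphasis.

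State in the same place that the percentage means *raised the theme in the interview* and is not an estimate of how many patients hold the view, because follow-up is tailored and questions may be skipped.

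The cost is a little more tabulation from coding already planned, and the care needed in wording the percentage. No new data are required. The 0.5% rule for creating nodes would remain weighted by volume of text. This change addresses what is reported for each node, not how nodes arise.

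### The 50 participants are justified only for the interviews, yet they also carry regressions not labelled exploratory, where logistic fits may separate and an unrestricted search makes chance findings likely

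*Protocol*

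**What the plan says.** Section 11.0 gives two reasons for the sample size. The first is saturation: "one should only conduct qualitative interviews to the point of saturation". The second is a rule of thumb: "It has been suggested that for observational studies, between 30-50 participants is the recommendation", cited to a chapter on designing qualitative research. It then concludes: "The sample size for this study is 50 participants". No effect size, event rate, precision or power is given.

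Section 7.0 adds a quantitative component, "urine drug screen results for opioids, cocaine, amphetamines, cannabis and benzodiazepines", taken "from medical records for a period of 12 months after study enrolment". Co-substance use also belongs to the secondary objective (Section 6.1) and appears under the secondary outcome measures (Section 10.0).

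Section 16.0 states the analysis of these data: "we will conduct linear and logistic regressions to see if there are any differences", relating substance use to socio-demographic characteristics. The form of the model is left open: "We will need to see the distribution of the outcomes to decide on whether a linear or logistic model will be appropriate". The section does not list the covariates for the regressions, does not say whether the substances are modelled separately or combined, and does not call the regressions exploratory.

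**The concern.** The sample size and one of the analyses rest on different footings. A saturation argument says when new interviews stop adding perspectives. It says nothing about how well 50 people can estimate associations between personal characteristics and drug-screen results. Because Section 11.0 attaches the 30–50 range to observational studies in general, a reader could take it as cover for the regressions too.

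Two separate problems could follow.

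- **Separation.** In a sample of 50, a small category may contain no positive participants, or only positive ones. Maximum-likelihood logistic regression then has no finite estimate for that category. Where it does have one, small samples push odds ratios away from 1.
- **Chance findings.** Looking for any difference across several substances and characteristics, with no limit on the number of comparisons and no exploratory label, makes it likely that something reaches p < 0.05 by chance.

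**Working it through.** **The plan's own figure.** There is no calculation to reproduce. Fifty is the top of the quoted 30–50 range.

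**Inputs from the Protocol.** N = 50; five substances; 56% men in the sponsor's earlier cohort (Section 5.1), so about 28 and 22 of 50.

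**Assumptions, because the Protocol gives no values.** Positivity 10% to 40% per participant; ethnicity as two groups with 20% in the smaller; treatment type, if used, in three groups of 70/20/10%; age continuous; two-sided 0.05; no true association.

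**Step 1: what 50 people can detect.** With a 28/22 split and 80% power, the smallest detectable contrast is about 30% versus 69%:

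odds ratio = (0.69/0.31) / (0.30/0.70) ≈ 5.2

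Events per coefficient in a model with five coefficients are 50 × p / 5, which gives 1, 2 and 3 at 10%, 20% and 30% positivity.

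**Step 2: separation, if the outcome is a yes/no per participant.** Null data were simulated at N = 50, and each sample was tested for complete or quasi-complete separation by linear programming.

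| Model | 10% | 20% | 30% | 40% |
|---|---|---|---|---|
| Sex, age, binary ethnicity | 47% | 13% | 4% | 2% |
| The same plus three-level treatment type | 85% | 49% | 29% | 21% |

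Independent repeats agreed within a few percentage points.

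A hand check for treatment type alone at 20% positivity: the 10% group has no positive participant with probability (1 − 0.10 × 0.20)^50 = 0.98^50 = 0.36, and the 20% group with probability 0.96^50 = 0.13. At least one of the two has none with probability about 1 − (0.64 × 0.87) = 0.44, close to the 46% simulated for treatment type alone.

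Sex alone separates in 14% of samples at 10% positivity and in about 1% or fewer at 20% and 30%. The risk therefore comes from sparse categories and rare outcomes.

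**Step 3: chance findings.** For k independent tests at 0.05, the chance of at least one false positive is 1 − 0.95^k:

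- k = 5 (one per substance): 23%
- k = 15: 54%
- k = 25 (five substances by five characteristics): 72%, with 25 × 0.05 = 1.25 expected

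The five characteristics are borrowed from the list that Section 16.0 gives for displaying themes, since none is given for the regressions.

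The alternative to the formula is to simulate whole null studies, with five yes/no outcomes at 10, 20, 30, 50 and 70% positivity. At least one Wald p < 0.05 appeared in 46% with a four-coefficient model and in 33% with a six-coefficient model. Separated fits were left out, which partly explains why these figures are below the formula.

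**The case against.** The case on the other side is substantial, and several parts of it stand.

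- **A reader might infer that many models will fail.** The documents do not support that. The high separation figures depend on an assumed three-level treatment split. The regression sentence names socio-demographic variables only; type of treatment appears in the preceding statement about displaying themes. Without it, separation is about 13% or less from 20% to 40% positivity.
- **A reader might infer five ordinary logistic models, one per substance.** The text says linear and logistic, with the choice still open, and does not say how the substances are handled. With 12 months of screens, a proportion of positive screens is an equally open outcome, and a linear model of it cannot separate.
- **The 72% is an upper illustration.** It assumes 25 independent tests from a borrowed list that includes both sex and gender, which overlap heavily.
- **The two problems do not add up.** A separated coefficient usually has a very large Wald standard error, so it tends to hide an association rather than create a false one.
- **Sizing a qualitative study on its primary aim is normal.** This also stands, and N need not change.
- **Covariate coding and multiplicity rules may sit in an analysis plan that is not shown.** Their absence from the Protocol is not the complaint. The basis for N, and an open-ended search with no exploratory label, are in the Protocol itself.

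**Conclusion.** The point holds in a conditional form. Section 11.0 supports 50 participants for the interviews and gives no basis for the regressions in Section 16.0.

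If a participant-level yes/no outcome is chosen, a standard logistic fit may separate. The risk runs from about 2% (compact model, 40% positivity) to about 85% (three-level treatment type added, 10% positivity). It is nil for a continuous outcome. An unrestricted search carries a 23% to 72% chance of at least one false positive for 5 to 25 independent tests, and 33–46% in the simulated null studies. All positivity rates, and all category splits other than sex, are assumptions.

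The documents do not show that the models will fail, that chance results will be presented as established, or that the study needs more participants. The qualitative primary aim is unaffected. The change is still worth making, because a bias-reduced method with an exploratory label is safer at this size and costs little.

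**What to change.** Keep N = 50.

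1. **Section 11.0:** state that the 30–50 range and the saturation argument support the interviews only, and that the regressions were not sized.
2. **Section 16.0:** for any participant-level binary outcome, use Firth (bias-reduced) logistic regression, which gives finite estimates under separation and reduces the small-sample bias.
3. **Section 16.0:** merge sparse categories before fitting, for example to at least 10 participants per level. Merging alone is not enough: a level of 10 still has no positive participant with probability 0.8^10 = 0.11 at 20% positivity and 0.9^10 = 0.35 at 10%. That is why the Firth method is also needed.
4. **Section 16.0:** label the regressions exploratory, and report estimates with 95% confidence intervals and no significance claims.

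The cost is wording in two sections and the loss of some fine categories. Recruitment and data collection do not change.

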### **17.0 Data Monitoring**

The main concern for this study data is the non-physical risks associated with a loss of privacy or confidentiality. Procedures have been put into place that are designed to keep your information confidential. The consent form and any study identifiers will be stored securely and separately from the collected information. This study does not require data and safety monitoring board due to the reasons described above in a social/behavioral research type of study.

